	**Prognostic factors**									
		Sociodemographic data (Sociodemographic questionnaire)		X						
	**Potential confounding factors**									
		Complications during surgery (Surgical report)			X^f^					
		Postoperative complications (Postoperative medical notes)						X^f^				
	**Process measures**									
		Protocol adherence (Adherence questionnaire)							X	
	**Cost measures**									
		Care program (Bottom-up approach)		X^f^						
		Health care utilization (Cost questionnaire)							X	X
		Informal care (Cost questionnaire)							X	X
		**Productivity loss**								
			Presenteeism: iPCQ^g^ and WHO-HPQ^h^	X		X	X	X	X	X
			Absenteeism: iPCQ	X		X	X	X	X	X
			Unpaid productivity: Cost questionnaire						X	X

^a^T_0_: 1 month before surgery; T_1_: 1 week after surgery; T_2_: 3 weeks after surgery; T_3_: 6 weeks after surgery; T_4_: 3 months after surgery; T_5_: 6 months after surgery.

^b^PROMIS: Patient-Reported Outcomes Measurement Information System.

^c^IPAQ: International Physical Activity Questionnaire.

^d^RI-5: recovery specific quality of life questionnaire short form.

^e^VAS: visual analog scale.

^f^Measured by the research team.

^g^iPCQ: Institute for Medical Technology Assessment (iMTA) Productivity Cost Questionnaire.

^h^WHO-HPQ: World Health Organization—Health and Work Performance Questionnaire.

#### Prognostic Factors

Before surgery (T_0_), various sociodemographic data will be assessed (sex, age, level of education, living conditions, working conditions) and questions asked regarding expectations about the length of recovery. Also the T-scores of the PROMIS physical functioning short forms conducted by the patient will be calculated.

#### Potential Confounding Factors

Major complications during surgery (eg, conversion to an open procedure), major complications in the postoperative course (eg, leading to a prolonged hospital stay of more than 2 nights after surgery), and readmission to the hospital in the 30 days after surgery or repeated surgery in the 30 days after surgery are considered as potential confounders. The complications will be assessed by reviewing the surgical reports and postoperative notes.

#### Process Measures

A process evaluation of the intervention will be carried out in accordance with the Linnan and Steckler method [39]. Table 3 contains the different components of the intervention and the level at which they are measured and in what way.

**Table 3 table3:** Process evaluation.

	Website	App	eConsult	Telephone consult after 2 weeks	Activity tracker
Reach: The proportion of intended target audience that participated in the study	Patients who met the inclusion criteria, signed informed consent, and are randomized to the intervention or control group^a^						
Dose delivered: The number or amount of intended units of each component delivered or provided to the intervention group	Proportion of the patients of the intervention group who received an account for the web portal and app^a^			Proportion of the patients of the intervention group who received a telephonic appointment at discharge^b^	Proportion of the patients of the intervention group who received an activity tracker^a^
Dose received: The extent to which participants from the intervention group actively engage with, interact with, are receptive to, or use materials or recommend resources	Proportion of the patients of the intervention group that made a convalescence plan^c^	Proportion of the patients of the intervention group that used the app^d^	Proportion of the patients of the intervention group that asked one or more questions on the web portal^c^	Proportion of the patients of the intervention group that received their telephonic appointment^b^	Proportion of the patients of the intervention group that connected the activity tracker to their phone^c^
Fidelty: The extent to which the intervention was delivered as planned	Proportion of the convalescence plans that are electronically approved by the specialist^c^	X	Proportion of the questions that were answered^c^	Proportion of the patients of the intervention group that came back at the outpatient office in addition to their telephonic consult^b^	Proportion of the patients of the intervention group that used the activity tracker in the first 3 weeks after surgery (minimum 3 days per week) and in the sixth week after surgery (minimum 3 days)^c^
Participant attitudes: Satisfaction and usage barriers of the intervention	Assessment of the website by the intervention group and reasons for not using the website^d^	Assessment of the app and reasons for not using the app^d^	X	X	Assessment of the activity tracker and reasons for not using the activity tracker^d^

^a^Data collection method: logistic database.

^b^Data collection method: notes in the medical record.

^c^Data collection method: web log.

^d^Data collection method: adherence and satisfaction questionnaire.

#### Cost Measures

##### Identification of Costs

Costs will be measured from a societal and a health care perspective. Societal costs will consist of costs of the intervention (ie, the substitution of perioperative care by eHealth), other health care use, informal care, absenteeism (ie, absence from work), presenteeism (ie, reduced productivity while at work), and unpaid productivity (ie, inability to perform educational activities, chores, volunteer work). When the health care perspective is applied, only costs accruing to the formal health care sector will be included (ie, costs of the intervention and other health care use).

##### Measurement and Valuation of Costs

Intervention costs will include all costs related to the development and implementation of the intervention and will be measured using a bottom-up microcosting approach (ie, detailed data will be collected regarding the quantity of resources consumed during the development and implementation of the intervention as well as their unit prices). All other cost categories will be measured using Web-based questionnaires administered at baseline and after 1 week, 3 weeks, 6 weeks, 3 months, and 6 months of follow-up (Table 2). Health care costs will include costs related to the use of primary care (eg, general practitioner), secondary care (eg, hospital visits), and medication. These costs will be valued using Dutch standard costs and, if unavailable, prices according to professional organizations [40]. Informal care will be valued using a recommended Dutch shadow price [40]. Absenteeism will be measured using the Institute for Medical Technology Assessment (iMTA) Productivity Cost Questionnaire (iPCQ) and valued in accordance with the friction cost approach using the estimated cost of productivity losses in the Netherlands [40,41]. Presenteeism costs will be measured using the iPCQ questionnaire and the World Health Organization Health and Work Performance Questionnaire and valued using the estimated cost of productivity losses in the Netherlands as well [42]. Unpaid productivity costs will be valued using the aforementioned recommended Dutch shadow price [40].

### Sample Size Calculation

Previous studies evaluating this type of intervention on RNA are lacking. We based our sample size calculation on the outcomes on RTW after gynecological surgery of our previous study [16]. Based on this study we expected a hazard ratio (HR) of 1.4 for RNA using the optimized intervention. Considering an HR of 1.4 and using a 2-sided log-rank test at a significance level of 5%, we need to observe 285 events (patients returning to normal activities) to achieve a power of 80%. The total sample size is set at 308 (154 per arm) to account for an anticipated proportion of 2.5% of patients not returning to daily activities within the 6-month follow-up period and a dropout rate of 5%.

### Recruitment and Inclusion

All patients between 18 and 75 years old who are on the waiting list for a laparoscopic cholecystectomy, inguinal hernia surgery, or adnexal surgery in one of the participating hospitals who meet the inclusion criteria will receive a letter of information about the study on behalf of their doctor. After 1 week, contact will be made by phone to evaluate their willingness to participate and to access eligibility. If the patient wants to and is eligible to participate, informed consent will be signed. Participants will not receive any financial or nonfinancial incentives.

### Allocation

After inclusion, patients will be asked to complete the first online questionnaire (T_0_) within the month before surgery. After patients have completed the questionnaire, randomization will take place by means of a computer-based randomization list stratified regarding hospital, sex, and surgical procedure using permuted blocks, size 2. Patients are randomized to the intervention or the control group in a 1:1 ratio. The researcher performing randomization is independent from the recruitment or data analyses.

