###### Postoperative Consult by eConsultation Instead of Consultation in the Outpatient Clinic

At discharge, patients from the intervention group will not receive a standard appointment at the outpatient clinic. Instead, they are offered continuous guidance via the website (information, feedback on recovery) and the possibility to ask questions on the website to a health care professional from their own hospital by means of an eConsult in case of recovery problems (Figure 6). They are informed that the question will be answered within 2 working days except for urgent matters. In that case, they receive a phone number for direct contact. In addition patients will receive a telephone call 2 weeks after surgery to inform them about any test results. Various studies already have proven that telephone follow-up is feasible and effective after the type of surgical procedures which are included in this study [26-28]. The telehealth follow-up aims to replace the standard single postoperative consultation in the outpatient clinic to increase access to care, reduce patient uncertainties and fear related to the recovery process, reduce costs and workload, and meet patient preferences of care during out-of-office hours [29,30]. We hypothesize that patients will be more comfortable and less hampered in resuming their activities with the opportunity to ask questions whenever they prefer instead of the standard consultation several weeks after surgery.

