### Blinding

Patients are blinded to the intervention as they do not know which program is developed as a nonintervention or intervention care program. After allocation, patients will receive an email containing a link to the care program to which they are allocated. Both care programs can be accessed through the website, but after signing in, patients will receive access only to the part of the website to which they are randomized. The researchers involved in the analyses will be blinded to the allocation throughout the analyses. Health care providers cannot be blinded to the intervention because it is highly likely that they will be notified of the allocation either by the patient or the patient’s medical file.

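### Fixed blocks of 2 within small local strata make the second allocation of each pair certain to anyone who knows the block size and the previous allocation, so concealment is weakened

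*Protocol article*

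**What the plan says.** The protocol article (Allocation) fixes a single block size: the list is "stratified regarding hospital, sex, and surgical procedure using permuted blocks, size 2". It adds that "Patients are randomized to the intervention or the control group in a 1:1 ratio".

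Two safeguards are given in the same section. One concerns timing: "After patients have completed the questionnaire, randomization will take place by means of a computer-based randomization list". The other concerns the person: "The researcher performing randomization is independent from the recruitment or data analyses".

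Blinding states that "Health care providers cannot be blinded to the intervention" and gives the reason: "it is highly likely that they will be notified of the allocation either by the patient or the patient’s medical file". Two features of the intervention also reveal the arm:
- The operating surgeon approves the convalescence plan electronically on the first postoperative day (Making a Personalized Convalescence Plan).
- At discharge, "patients from the intervention group will not receive a standard appointment at the outpatient clinic".

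On entry, Recruitment and Inclusion describes a letter sent in the name of the patient's doctor. A week later, "contact will be made by phone to evaluate their willingness to participate" and to check eligibility. The article does not say who calls. The exclusion criteria include severe comorbidity that might complicate the postoperative course.

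The article does not say that the block size is withheld from sites, or that those who invite and screen are kept unaware of earlier allocations.

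**The concern.** A permuted block of 2 with equal allocation can only run intervention–control or control–intervention. The first assignment therefore fixes the second. An independent person holding the list does not change this, because the next assignment is deduced from the last one and not read from the list.

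The strata are local and few in each hospital, so the last allocation in a stratum is easy to keep track of. If it is known to someone who can influence invitation, eligibility or order of entry, patients expected to recover quickly or slowly can be steered between arms. The comorbidity exclusion matters here because it is a judgement about the postoperative course, and so about the primary outcome, time to return to normal activities. Bias of this kind enters before randomisation. Intention-to-treat analysis does not remove it, and covariate adjustment does so only as far as the selection runs through measured variables.

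**Working it through.** **Inputs.** Block size 2, 1:1, stratified by hospital, sex and procedure (Allocation). 7 hospitals (Study Setting). 308 patients (Sample Size Calculation). The plan's total reproduces from its own inputs: 285/(0.975 × 0.95) = 307.7, rounded up to 308. The block size does not affect it.

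**Strata.** Assume that adnexal surgery occurs only in women and that each of the three procedures is one level. Each hospital then has 2 procedures × 2 sexes + 1 = 5 strata. In total 7 × 5 = 35, with 308/35 = 8.8 patients each on average. Nominally there are 7 × 2 × 3 = 42, with 7.3 patients each.

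**Certain allocations with blocks of 2.** A stratum of n patients has floor(n/2) determined allocations.
- Ceiling, if every block is complete: 308/2 = 154 (50%).
- If stratum sizes are Poisson with mean m, the expected number per stratum is m/2 − (1 − e^(−2m))/4. With m = 8.8 this is 4.40 − 0.25 = 4.15, and 35 × 4.15 = 145 (47%). With 42 strata it is about 144.

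**Complete blocks of known fixed size 2b.** The share of certain allocations is 1/(b + 1). The expected number of correct guesses per block, always guessing the arm that lags, is b + (4^b/C(2b,b) − 1)/2.

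| Block size | Certain | Correct guesses |
|---|---|---|
| 2 | 50% | 1.5/2 = 75% |
| 4 | 33% | 2.833/4 = 71% |
| 6 | 25% | 4.1/6 = 68% |

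Chance alone gives 50%.

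**A stratum of 9 patients**, close to the average of 8.8. With fixed blocks of 2, certain allocations are 4/9 = 44% and correct guesses (4 × 1 + 5 × 0.5)/9 = 72.2%. The mixed schemes come from exact enumeration of all sequences. The observer knows which sizes are possible but not their order, and each size is equally likely.

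| Scheme | Certain | Correct guesses |
|---|---|---|
| Fixed 2 | 44% | 72.2% |
| Random 2 and 4 | about 9% | 69.6% |
| Random 4 and 6 | about 6% | 66.2% |

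For comparison, fixed blocks of 4 give 68.5% correct guesses: two blocks at 2.833 plus one guess at 0.5, divided by 9. Mixing 2 and 4 therefore removes most of the certainty but does not beat fixed 4 on guess rate. Mixing 4 and 6 improves on fixed 2 and fixed 4 in both respects.

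**The case against.** The strongest reply is that prediction needs three things in one person: knowledge of the block size, knowledge of the latest allocation in that stratum before the next patient enters, and influence over entry. The article places them together in nobody. All eligible waiting-list patients receive the letter. Randomisation waits for consent and the baseline questionnaire, so the patient's own completion date helps to set the place in the block. The documented signs of allocation arise on the first postoperative day and at discharge, which can be up to about a month after randomisation. By then the block partner may already be allocated. Small blocks also have a rationale with about 9 patients per stratum.

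Much of this stands, and it is why the finding is conditional. The timing argument is only partial. Inclusion was planned from September 2015 to August 2016, about 12 months. With 8.8 patients per stratum, entries are on average 12/8.8 = 1.4 months apart (assuming even accrual and equal strata). That is longer than the month within which baseline and surgery fall. The article also says that providers may hear of the allocation from the patient, without giving a time.

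Strengths and Limitations argues that unblinded professionals will not affect the results because they have little part in the intervention or data collection. That does not address selection at entry.

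A reader might infer two stronger claims that the article does not support:
- That concealment failed and half the allocations were in fact foreseen. No passage says that recruiters knew the block size or the earlier allocations.
- That the self-reported primary outcome is unblinded, which would compound the problem. Blinding describes patients as not knowing which programme is the intervention. One may doubt how well that works, but the selection concern does not depend on it.

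**Conclusion.** The point holds in conditional form. The stated scheme makes the second allocation of every pair certain to anyone who knows the block size and the previous allocation in the stratum. The number exposed is at most 154 of 308, and about 145 under Poisson stratum sizes. Both figures assume complete and timely knowledge, so they are upper limits on what could be exploited and not estimates of what was. Given providers who are expected to learn allocations and a judgement-based exclusion, concealment is weakened but not shown to be broken. The two stated safeguards do not close this route. The size of any resulting bias cannot be computed from the document. The sample size and event count are unaffected.

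**What to change.** **For any allocations still to be made:** regenerate the list with randomly varying block sizes, for example 4 and 6. Withhold the sizes from sites and recruiters, and state who knows the scheme. Predictability falls but does not vanish. The cost is a new list and somewhat more imbalance in unfinished blocks: at most 3 patients in a stratum with a block of 6, against 1 with a block of 2. The planned adjustment for hospital, procedure and sex (Effect Analyses) covers this.

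**For patients already randomised, or if enrolment is complete** (the expected end was August 2016):
- Report the fixed block size, and which staff knew it and the earlier allocations, as a limitation.
- Compare baseline PROMIS physical functioning T-score and recovery expectation between first-in-block and second-in-block patients, by arm. Both are collected before surgery (Prognostic Factors), so no new data are needed.

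The check has limits. With about 154/2 = 77 first-in-block and 77 second-in-block patients per arm, and an assumed T-score SD of 10, the difference detectable with 80% power at two-sided 5% is about 2.80 × 10 × √(2/77) = 4.5 points. A null result therefore does not exclude modest selection, or selection on unmeasured features.

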### Blinding

Patients are blinded to the intervention as they do not know which program is developed as a nonintervention or intervention care program. After allocation, patients will receive an email containing a link to the care program to which they are allocated. Both care programs can be accessed through the website, but after signing in, patients will receive access only to the part of the website to which they are randomized. The researchers involved in the analyses will be blinded to the allocation throughout the analyses. Health care providers cannot be blinded to the intervention because it is highly likely that they will be notified of the allocation either by the patient or the patient’s medical file.

### Data Collection

Data will be collected by means of self-reported electronic questionnaires at standard moments. Data will be collected in the month before surgery (T_0_) and 1 week (T_1_), 3 weeks (T_2_), 6 weeks (T_3_), 3 months (T_4_) and 6 months (T_5_) after surgery (Table 2). When data regarding RNA are missing during 2 measuring moments, an attempt will be made to collect the missing questions by telephone or email.

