#### Primary Outcome

The primary outcome measure of the study will be time to return to normal activities (RNA). The Patient-Reported Outcomes Measurement Information System (PROMIS) Physical Functioning item bank version 1.2 will be used to measure limitations in daily activities. This item response theory (IRT)–based item bank has been developed and validated in the United States and translated into Dutch-Flemish [31,32]. Initial validation studies in Dutch patients confirmed the unidimensionality and underlying calibration of the IRT model (personal communication, article submitted). This item bank consists of 121 activities. We made a selection of the 29 most relevant activities for this study (Multimedia Appendix 2). We considered the 92 excluded activities as not being affected by the type of surgery (eg, “Can you brush your hair?”) or as duplicate activities. The list of 29 activities will be presented to the patients at baseline (prior to surgery), and they will be asked to select 8 activities which are most relevant for them in daily life. In this way, patients will design their own personal physical functioning short form. Since items in an IRT-based item bank are calibrated onto the same continuum, one can select any subset of questions in that bank and the scores obtained from the derived short forms are comparable to that from the complete bank [33]. In the follow-up questionnaires, patients will only receive those PROMIS questions regarding the 8 activities that they selected before surgery as relevant to their personal life. Items are scored on a 5-point scale with 1 as most limited and 5 as no limitation. In addition, they will be asked postoperatively whether they can perform this activity on the same level as before surgery. If they answer “yes,” they are asked to fill in since when (date), and the question will no longer be repeated in the following questionnaires. If the question is answered with a “no,” the question will be asked again at the next follow-up moment. For each patient, this will result in 8 dates of resumption of their activities. These dates will be converted into time periods by calculating the number of days that have elapsed between the date of surgery and the date of the resumption of that particular activity. The moment of resumption of the last activity on the list will be defined as the RNA moment and thus the primary outcome measure will be time elapsed between surgery and resumption of the last activity. If patients have not resumed 1 or more activities at 6 months, those activities will be censored. If information about the resumption of 2 or fewer activities is missing, the RNA moment will be calculated based on 6 activities. If information about the resumption of more than 2 activities is missing, the RNA moment cannot be calculated accurately and will be considered as missing data.

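### The retrieval rule for missing return-to-normal-activities (RNA) data does not reach a patient who has an activity still open at 3 months and misses only the 6-month form

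*Protocol article*

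**What the plan says.** Follow-up questionnaires are sent at "1 week (T_1_), 3 weeks (T_2_), 6 weeks (T_3_), 3 months (T_4_) and 6 months (T_5_) after surgery" (Data Collection). Nothing follows T5. The only stated condition for active retrieval is in the same section: "When data regarding RNA are missing during 2 measuring moments, an attempt will be made to collect the missing questions by telephone or email".

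The Primary Outcome section defines what can be missing. For each of the 8 chosen activities: "If they answer “yes,” they are asked to fill in since when (date), and the question will no longer be repeated in the following questionnaires". An activity answered no comes back on the next form. The endpoint depends on the slowest activity: "the primary outcome measure will be time elapsed between surgery and resumption of the last activity".

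That section has three rules for incomplete resumption data:

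- An activity still unresumed at 6 months is treated as a censored observation.
- For one or two activities without resumption data, the rule is: "If information about the resumption of 2 or fewer activities is missing, the RNA moment will be calculated based on 6 activities".
- With three or more such activities, the patient's primary outcome is set to missing.

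**The concern.** A single missed form at T1 to T4 largely repairs itself, because the question comes back on the next form and asks for a date. A missed T5 has no next form. The two-moment trigger treats both cases alike, so it gives no rescue at the one point where nothing else can recover the date.

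The patients who lose primary-outcome data this way are not a random subset. Because the question stops after a yes, RNA data can be missing at T5 only for someone with an activity still open. If T5 is the only missed form, that person answered no at 3 months.

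The handling rules then matter. With one or two activities open, the missing-information rule would compute the RNA moment from the others and leave out exactly the activities that define the endpoint. The patient would carry an RNA date earlier than a form on which he or she reported not having returned to normal. Such a patient is not flagged as missing, so imputation of missing values would not reach the error. With more than two open, the patient drops out of the primary outcome.

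**Working it through.** **The plan's own figures.** Inputs from Sample Size Calculation: HR 1.4, two-sided 5%, 80% power, 285 events, N = 308, 2.5% not returned by 6 months, 5% dropout.

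- Freedman: (1.960 + 0.842)² × (2.4/0.4)² = 7.849 × 36 = 282.6, so 283 events.
- Schoenfeld: 4 × 7.849 / (ln 1.4)² = 31.40 / 0.1132 = 277.3, so 278 events.
- N: 285 / (0.975 × 0.95) = 307.7, so 308.

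Both event counts lie within 3% of 285, and N reproduces. Nothing below disputes these figures.

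**Does the trigger fire?** The wording does not require consecutive moments.

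| Pattern | Moments with RNA data missing | Trigger met? |
|---|---|---|
| All 8 resumed by T4, T5 skipped | 0 | Not needed |
| One of T1–T4 missed, T5 completed | 1 | No, but a later form asks again |
| An earlier form and T5 both missed, activity open | 2 | Yes |
| T1–T4 complete, activity open at T4, T5 missed | 1 | No, and no later form exists |

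Only the last row is the gap.

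**How many patients?** The article gives neither the share open at 3 months (s) nor the non-response per form (m). Assume s = 10–20% and m = 5–20%. Patients missing T5 with an activity open: 308 × s × m. Those who also completed T1 to T4, if non-response is independent between forms: 308 × s × m × (1 − m)⁴, where 0.95⁴ = 0.81 and 0.80⁴ = 0.41. The row for s = 15.8% comes from the plan's 2.5% still open at 6 months under exponential recovery times: √0.025 = 0.158.

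| s | m | 308 × s × m | × (1 − m)⁴ |
|---|---|---|---|
| 10% | 5% | 1.5 | 1.3 |
| 10% | 20% | 6.2 | 2.5 |
| 15.8% | 5% | 2.4 | 2.0 |
| 15.8% | 20% | 9.7 | 4.0 |
| 20% | 5% | 3.1 | 2.5 |
| 20% | 20% | 12.3 | 5.0 |

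For scale, the dropout allowance is 308 × 0.05 = 15.4 patients.

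**Power.** Φ(½√events × ln 1.4 − 1.96) gives 0.811 at 285 events, 0.804 after losing about 5 events, 0.797 after about 10 and 0.793 after about 12.

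**Bias.** A large-sample Cox simulation (200,000 patients) used exponential times, a true HR of 1.40, 2.5% open at 6 months overall, and non-response at T5 only, among patients open at day 91. Earlier forms are taken as complete, so 4.6 to 9.3 patients per 308 are affected, mostly more than the 1 to 5 above. For the counted-early column, their event dates were drawn evenly between days 21 and 91, which is an assumption.

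| T5 non-response, control / intervention | Dropped | Counted as earlier events | Censored at T4 |
|---|---|---|---|
| 10% / 10% | 1.39 | 1.39 | 1.40 |
| 20% / 20% | 1.37 | 1.37 | 1.40 |
| 20% / 10% | 1.34 | 1.34 | 1.40 |
| 20% / 5% | 1.32 | 1.33 | 1.40 |
| 10% / 20% | 1.43 | 1.42 | 1.40 |
| 5% / 20% | 1.45 | 1.44 | 1.40 |

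The last column holds when non-response is unrelated to the remaining recovery time.

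**The case against.** A reader might infer more than the text supports, in four ways.

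- *Everyone who misses only T5 is a slow recoverer.* Not so. Someone who resumed all 8 activities by T4 has nothing left to report and loses no primary-outcome data.
- *These patients are never contacted.* The article states one condition for a telephone or email attempt. It does not exclude routine questionnaire reminders, which may be in the full protocol. The gap is in the stated rule.
- *They are certain to be recorded as early events.* That depends on classing a no at T4, with no T5 form, as missing information. It can be argued that the T4 answer is information: not resumed by 3 months. The censoring rule does not settle this, because it concerns status at 6 months, which is unknown here. Even under the missing-information rule, the latest resumed activity may lie close to 3 months.
- *About 12 patients are lost, and the app and tracker skew response by arm.* The 12 includes patients who also missed an earlier form and so meet the trigger. Differential response is possible but not shown: instructed tracker wear ends in week 6, and both arms receive self-reported electronic questionnaires.

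It can also be said that the harm comes from the handling rules in Primary Outcome, not from the retrieval sentence. That is partly right, and is why the fix touches both sections. What stands is that the retrieval rule misses the one form that cannot repair itself, and that the article does not settle how the resulting data are classed.

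**Conclusion.** The point holds in a narrow form. Under the stated trigger, a patient with complete T1 to T4 forms, an activity open at 3 months and a missed T5 is not pursued, and the handling rules allow an RNA date that contradicts that patient's T4 answer. On the assumed rates this concerns about 1 to 5 of 308 patients, with about 12 as the ceiling if earlier forms are always completed.

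Power is hardly touched. The issue is bias in the late tail: slight attenuation when non-response is equal between arms, and a shift either way when it is not. The simulated extremes of 1.32 and 1.45 need a fourfold difference in non-response and complete earlier forms, so they bound the problem and do not predict it. All of this rests on assumed response rates and exponential times. It is a modest, avoidable weakness that is cheap to remove.

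**What to change.** - **Data Collection:** add that a telephone or email attempt is made after a missed T5 whenever at least one activity is still open.
- **Primary Outcome:** state that if the attempt fails, an activity last reported as not resumed counts as not resumed, and the patient's RNA time is censored at the last completed form. It is then neither computed from the remaining activities nor set to missing.

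Chasing every single missed form at T1 to T4 is not needed, since the next form asks again.

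The cost is a few extra contacts on top of the telephone and email attempts already planned, plus a sentence in each section. Sample size and design do not change. Resumption dates are asked retrospectively, so a late call can still recover them. The Results section says data cleaning and analyses have not begun, so the censoring rule can still be fixed before the data are analysed. Its remaining assumption, that T5 non-response is unrelated to remaining recovery time, should be stated with it.
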